# Testing a Biobehavioral Model of Chronic Stress and Weight Gain in Young Children (Family Stress Study): Protocol and Baseline Demographics for a Prospective Observational Study

**DOI:** 10.2196/48549

**Published:** 2024-06-20

**Keywords:** stress, child, preschool, adiposity, household chaos, cortisol, COVID-19, behavioral mechanisms, caregiver-child relationship quality

## Abstract

**Background:**

Chronic stress is an important risk factor in the development of obesity. While research suggests chronic stress is linked to excess weight gain in children, the biological or behavioral mechanisms are poorly understood.

**Objective:**

The objectives of the Family Stress Study are to examine behavioral and biological pathways through which chronic stress exposure (including stress from COVID-19) may be associated with adiposity in young children, and to determine if factors such as child sex, caregiver-child relationship quality, caregiver education, and caregiver self-regulation moderate the association between chronic stress and child adiposity.

**Methods:**

The Family Stress Study is a prospective cohort study of families recruited from 2 Canadian sites: the University of Guelph in Guelph, Ontario, and McMaster University in Hamilton, Ontario. Participants will be observed for 2 years and were eligible to participate if they had at least one child (aged 2-6 years) and no plans to move from the area within the next 3 years. Study questionnaires and measures were completed remotely at baseline and will be assessed using the same methods at 1- and 2-year follow-ups. At each time point, caregivers measure and report their child’s height, weight, and waist circumference, collect a hair sample for cortisol analysis, and fit their child with an activity monitor to assess the child’s physical activity and sleep. Caregivers also complete a web-based health and behaviors survey with questions about family demographics, family stress, their own weight-related behaviors, and their child’s mental health, as well as a 1-day dietary assessment for their child.

**Results:**

Enrollment for this study was completed in December 2021. The final second-year follow-up was completed in April 2024. This study’s sample includes 359 families (359 children, 359 female caregivers, and 179 male caregivers). The children’s mean (SD) age is 3.9 years (1.2 years) and 51% (n=182) are female. Approximately 74% (n=263) of children and 80% (n=431) of caregivers identify as White. Approximately 34% (n=184) of caregivers have a college diploma or less and nearly 93% (n=499) are married or cohabiting with a partner. Nearly half (n=172, 47%) of the families have an annual household income ≥CAD $100,000 (an average exchange rate of 1 CAD=0.737626 USD applies). Data cleaning and analysis are ongoing as of manuscript publication.

**Conclusions:**

Despite public health restrictions from COVID-19, the Family Stress Study was successful in recruiting and using remote data collection to successfully engage families in this study. The results from this study will help identify the direction and relative contributions of the biological and behavioral pathways linking chronic stress and adiposity. These findings will aid in the development of effective interventions designed to modify these pathways and reduce obesity risk in children.

**Trial Registration:**

ClinicalTrials.gov NCT05534711; https://clinicaltrials.gov/study/NCT05534711

**International Registered Report Identifier (IRRID):**

DERR1-10.2196/48549

## Introduction

Chronic stress is increasingly recognized as an important risk factor in the development of obesity [1]. Among children aged as young as 2-6 years, exposure to chronic stress, including parental divorce, parental depression, and household chaos has been associated with higher weight status and excess weight gain over time [2-4]. The COVID-19 pandemic fundamentally disrupted life for families and has been a key source of chronic stress for young children [5,6] and their parents [7].

While research suggests chronic stress is linked to excess weight gain in children, the biological or behavioral mechanisms are poorly understood [8]. Biologically, a central aspect of the stress response is the activation of the hypothalamic-pituitary-adrenal axis, leading to increased circulating cortisol levels [9]. Prolonged elevation of cortisol, a glucocorticoid, leads to increased adiposity, particularly abdominal adiposity, as well as increased appetite and preferences for high-fat and high-sugar foods [9]. Few studies have examined the association between cortisol and obesity among young children and most of this research has been cross-sectional [10-12]. Biological stress could be implicated in weight gain through complex pathways that develop over time; thus, longitudinal research is needed to elucidate the direction of these pathways [8]. Putative behavioral mechanisms linking stress with excess weight gain include consumption of energy-dense foods [13], eating for comfort [14], low physical activity [15], high screen time [16], and poor sleep [17]. However, research examining these mechanisms over time is sparse, particularly among young children [8]. Understanding these behavioral mechanisms, including the relative contributions of weight-related behaviors linking family stress and excess weight gain in children, can help inform behavioral targets for obesity interventions for young children who experience stress in the home.

In previous studies, researchers concluded that the damaging impact of stress can be buffered when children have supportive relationships with their caregivers [18-20]. The ability of parents to manage their own emotions during times of stress, that is, parental self-regulation, also influences their child’s stress response [21]. Epidemiologic [3] and laboratory [22] research suggests that, when exposed to similar stressors, females have stronger biological reactivity to stress compared to males. Further, low-income households and households with less educated parents are associated with higher-stress environments [23,24] and children from these families bear a disproportionate share of the burden of obesity [25]. These findings underscore the need to examine how child sex, caregiver-child relationship quality, and caregiver self-regulation and education may moderate the pathways linking stress and excess weight gain in children.

Building on this existing research, the primary objective of the Family Stress Study is to test the conceptual model (Figure 1), using longitudinal structural equation modeling (SEM), that exposure to chronic stressors is directly associated with higher adiposity among children and partly mediated through alterations in children’s cortisol production and weight-related behaviors. It is hypothesized that (1) chronic stress at baseline will be positively associated with children’s BMI *z* score and waist circumference (WC) at 1- and 2-year follow-up, (2) the association between chronic stress and children’s adiposity outcomes will be partially mediated by children’s cortisol levels and children’s weight-related behaviors, and (3) associations between children’s cortisol levels and weight-related behaviors will be bidirectional (modeled as a cross-lagged structure within the longitudinal design). The secondary objective of this study is to examine the extent to which child sex, caregiver-child relationship quality, caregiver education, and caregiver self-regulation, moderate the associations examined in objective 1. Based on previous research, it is hypothesized that associations between chronic stress, cortisol levels, weight-related behaviors, and adiposity will be stronger among (1) children with less supportive caregiver relationships as compared to those with more supportive relationships [18,19], (2) female children as compared to male children [3,22], (3) children whose caregivers have lower education as compared to children whose caregivers have higher education [23,24], and (4) children whose caregivers have lower self-regulation as compared to children whose parents have higher self-regulation [21].

**Figure 1 figure1:**
[figure not shown]
Conceptual model for the Family Stress Study: a prospective observational study of biological and behavioral pathways linking stress and
child adiposity in young children.

The variables depicted in Figure 1 will be assessed across 3 time points, measured 1 year apart, which will allow the elucidation of the direction and the relative contributions of the complex biological and behavioral pathways linking chronic stress and adiposity. Study results will help inform interventions to modify these pathways and reduce obesity risk among young children in the post–COVID-19 context. This paper describes the approach, protocol methods, and baseline demographics of the participants enrolled in the Family Stress Study.

## Methods

### Study Design

The Family Stress Study is a prospective cohort study of children aged 2-6 years recruited from 2 Canadian sites: the University of Guelph in Guelph, Ontario, and McMaster University in Hamilton, Ontario. Ethics approval was obtained before the restrictions due to the COVID-19 pandemic were enacted in Ontario in March 2020, but recruitment had not begun. The original protocol, which included an in-person health assessment of adiposity using air displacement (bod pod) and researcher-led measures of child and caregiver height, weight, and child WC, was revised to a caregiver-led at-home health assessment of child and caregiver weight, height, and child WC to adhere to the COVID-19 safety protocols. Measures of COVID-19–related stress were added to the web-based health and behaviors survey. The revised protocol was approved by both research ethics boards. Figure 2 provides an overview of this study’s design.

**Figure 2 figure2:**
[figure not shown]
Design of the Family Stress Study for remote recruitment and data collection to test a biobehavioral model of chronic stress and weight gain in young children.

### Study Participants and Recruitment

Between July 2020 and December 2021, participants were recruited from the city of Guelph, the city of Hamilton, and surrounding areas. Recruitment was conducted primarily via the web using paid advertisements on Facebook (Meta) and Instagram (Instagram from Meta), and social media posts, including posts by community organizations that serve families, and through posters in community locations, including libraries and toy stores. All methods of recruitment provided caregivers with study contact information and directed them to this study’s website, where caregivers obtained additional details regarding this study’s process and interested caregivers completed an eligibility screener.

To be eligible to participate, families had to have at least one child aged 2-6 years and have no plans to move from the area within the next 3 years. Participants were excluded if they were (1) enrolled in the Guelph Family Health Study (a longitudinal study led by the investigative team) at the University of Guelph to allow data to be merged across the 2 studies; (2) children born preterm (before 34 weeks gestation); (3) children with any health condition expected to affect cortisol production, obesity, or growth or body composition (eg, Prader Willi syndrome and Cushing disease); and (4) children taking steroid medications, including oral or inhaled corticosteroids, medications for attention-deficit/hyperactivity disorder, or antidepressants or antipsychotic medications.

To participate, caregivers had to live with the child at least 50% of the time and could include parents (biological, related, adoptive, or foster), grandparents, aunts, and uncles. The primary caregiver was the caregiver who first signed up for this study and served as the main contact for the family. Eligible primary caregivers completed a web-based consent to enroll themselves and their oldest eligible child in the target age range (2-6 years). Primary caregivers provided contact information for themselves and, if applicable, an email address for a second caregiver. The secondary caregiver was contacted separately to enroll and complete web-based consent. Study coordinators also connected regularly with families via email, text, or phone to provide them with support throughout the data collection process.

### Ethical Considerations

This study was approved on March 11, 2020, and the amended protocol for remote data collection was approved by the University of Guelph Research Ethics Board (11-19-047) on June 12, 2020. The Hamilton Integrated Research Ethics Board approved this study on July 7, 2020, along with approval for the amended protocol on July 20, 2020 (10763). Recruitment and data collection began in July 2020 (Guelph) and August 2020 (Hamilton); primary caregivers enrolled in this study provided informed consent for themselves and their oldest eligible child and secondary caregivers provided informed consent for themselves. All participant data will be deidentified and only group data will be presented in all reports of this study’s results. At each data collection time point, participating families receive a CAD $25 grocery gift card per caregiver for completing a health and behaviors survey (also includes the diet recall for the child), and a CAD $30 grocery gift card per family for completing the at-home health assessment as a thank you for their time.

### Data Collection

Chronic stress and children’s weight-related behaviors including diet and physical activity or sleep, cortisol levels, and adiposity are assessed at baseline, 1- and 2-year follow-ups. Further, 1-year intervals for assessment are based on Canadian health practice guidelines that recommend measuring height and weight once per year for children aged 2 years and older [26]. At each time point, primary caregivers complete a web-based health and behaviors survey with questions about family demographics, family stress, child weight-related behaviors, mental health, and their own weight-related behaviors. Secondary caregivers complete an abbreviated version of the health and behaviors survey focused on measures of stress and their own weight-related behaviors. Primary caregivers complete a web-based 1-day dietary assessment for their child. Caregivers complete anthropometric measures, collect a hair sample for cortisol analysis, and fit their child with an activity monitor for the at-home health assessment.

### Measures

#### Child Adiposity

Families are provided with the necessary materials (a nonelastic flexible tape measure and Seca 803 digital scale [Seca]) and detailed, illustrated instructions [27-29] to complete the at-home health assessment, including the child’s WC [30], height [31], and weight. Caregivers report the measurements using a web-based survey. This process has been validated among preschool-aged children in previous studies [27-29]. BMI *z* scores are calculated in R^22^ using the “zscorer” package, based on the World Health Organization child growth standards [32]. WCs are measured by a caregiver to the nearest 0.1 cm using a soft retractable tape measure at the top of the iliac crest as per the protocol in the Canadian Health Measures Survey [30].

#### Child Hair Cortisol

Hair samples are used to assess children’s chronic cortisol concentrations as an indicator of chronic biological stress. Primary caregivers are instructed to cut a lock of hair approximately 1 cm in width from the posterior vertex [33], as close as possible to the scalp, and secure it to a collection card with the scalp end identified. Using hair to assess cortisol is more reproducible than other physiological measures, for example, saliva, because it aggregates day-to-day variations in hypothalamic-pituitary-adrenal axis activity, thereby reflecting chronic rather than acute stressful exposures [34,35]. Hair samples are sent for cortisol analysis at the Centre for Studies on Human Stress, Montreal, Quebec, a laboratory focused on analyzing stress hormones.

The Centre for Studies on Human Stress analyzes 3 cm of hair, representing approximately 3 months of stress exposure [36]. In brief, a 25 mg sample of hair is placed in a vial to which 2.5 mL of isopropanol is added and mixed for 3 minutes on a plate rotator. This wash procedure is repeated once, and hair samples dry overnight. Then, the washed hair is transferred to a new vial to which 1.5 mL of pure methanol is added and vials are rotated for 24 hours. Samples are spun in a centrifuge for 2 minutes at 10,000 rpm and 1 ml of the clear supernatant is transferred into a new vial. Methanol is then evaporated under a constant stream of nitrogen at 60°C for 20 minutes or until dry. When dried, 0.4 mL of phosphate buffer (CAL A, IBL-Hamburg) is added to the tube, and then vortexed for 15 seconds [37]. A commercially available immunoassay with chemiluminescence detection from IBL-International is used to determine cortisol concentrations. The ranges of assays at 0.015-3.20 µg/dL are converted to picograms or milligrams for reporting.

### Chronic Stress

Chronic stress is assessed using 5 different measures of stress: household stress, food insecurity, caregiver depression, children’s negative life events, and COVID-19–related stress. Household stress is quantified using the 15-item Confusion, Hubbub, and Order Scale (CHAOS) [38]. Primary caregivers respond to items including “you can’t hear yourself think in our home” or “there is very little commotion in our home” on a 4-point Likert scale from 1 (very much like your own home) to 4 (not at all like your own home). After reverse scoring relevant items, a total score will be calculated by summing the responses. The full CHAOS score [39-41], as well as the Emotional CHAOS subscale [4], created using 8 of the full-scale items, have been associated with obesity risk and obesogenic eating behaviors among young children. Standardized Cronbach α for the CHAOS survey was found to be 0.78 in the Guelph Family Health Study [42], which is a longitudinal study of families with toddlers and preschoolers [43].

Food security is examined using the Household Food Security Survey Module, an 18-item measure that includes 10 items that assess uncertain, insufficient, or inadequate food access related to adults in the household and 8 items focused on children over the previous 12 months [44]. Households will be categorized based on the total number of positive responses: food secure households (0 responses), marginally food insecure households (1 responses), moderately food insecure households (2 to 5 responses), or severely food insecure households (≥6 responses). While evidence for an association between food insecurity and obesity risk in children has been mixed [45], food insecurity is a prevalent source of stress among families, affecting 1 in 6 Canadian children [46], and has been shown to be associated with poorer diets in children [47].

Caregiver depressive symptoms are assessed using the 20-item short-form Centre for Epidemiologic Studies Depression Scale (CES-D) [48-50]. Both the primary and second caregivers respond to statements about the previous week including “everything I did was an effort” and “I felt lonely.” Responses are to be scored as 0 (less than 1 day), 1 (1-2 days), 2 (3-4 days), or 3 (5-7 days) and, after reverse scoring relevant items, a total score out of 30 will be calculated by summing the responses. The standardized Cronbach α for the CES-D was found to be 0.88 for mothers and 0.80 for fathers of young children in the Guelph Family Health Study [51]. Parental depression assessed using CES-D has been found to be associated with obesity risk and obesity-related behaviors in children [51,52].

Children’s negative life events are reported using an abbreviated List of Threatening Experiences [53], an 8-item measure of negative life events, for example, divorce. Primary caregivers report negative events for their child across their lifetime (or for the past year on the follow-up surveys) by answering “yes” or “no” to whether or not their child has encountered various events, such as “divorce or separation of parents” or “severe disease or accidents.” The total score will be determined by summing the number of negative events. This measure has been found to be associated with obesity risk in children [54].

COVID-19–related stress is assessed by asking both the primary and secondary caregiver about quarantine or illness due to COVID-19, change in employment status due to COVID-19 (eg, loss of job and change in work hours per location), and employment in essential services (eg, first responder, health care worker, critical infrastructure worker, food production and supply, production, supply of medicine, hydro, and gas, and corrections). Given that COVID-19 disrupted home and work life among families with young children, measures assessing work conflict [55], financial insecurity [56], and parenting stress [57] are also included in the caregiver’s web-based survey. Work-to-family conflict is assessed using a 5-item scale adapted from Carlson et al [55]. Caregivers are asked questions including “my work keeps me from family activities more than I would like” and “when I am home from work, I am often too frazzled to participate in family activities or responsibilities.” Responses are on a 5-point Likert scale from 1 (strongly disagree) to 5 (strongly agree) [55]. A total score will be calculated by summing the responses.

Financial insecurity is evaluated using 2 items adapted from the measures by Gundersen and Boushey [56]: “during the past month, was there a time when you were worried you would not be able to pay the mortgage, rent or other bills on time?” and “are you worried about not being able to pay the mortgage, rent or other bills on time over the next 6 months?” to which caregivers respond “yes” or “no.” Families will be coded as financially insecure if they respond positively to either item.

Parenting stress is assessed by asking caregivers 12 items from the parenting distress domain of the short-form parenting index [58]. Items include “I feel trapped by my responsibilities as a parent/caregiver,” “there are quite a few things that bother me about my life,” and “having a child has caused more problems than I expected in my relationship with my spouse/partner (or male/female friend).” Responses are on a 5-point Likert scale from 1 (strongly disagree) to 5 (strongly agree). After reverse scoring relevant items, a total score will be calculated by summing the responses. The standardized Cronbach α in a similar sample was 0.86 among mothers and 0.78 among fathers [59].

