An incremental model-building approach similar to the recommended approach by Curran et al [80] will be used to test this study’s objectives. The first component in the model-building approach is the LGM of the trajectories across time for the variables’ chronic stressors (explanatory variable), child cortisol and child behavior (mediator variables), and child adiposity (outcome variable). Each variable has its own trajectory and includes an intercept (I), which refers to a baseline value, and a slope (S), which refers to change over time. Of particular importance is that individual child variation in these I and S parameters will be modeled. If any of these components are found to be not statistically significant, they are removed from the model. Typically, the I means and variances are significantly different from 0, but the S means may or may not depict significant linear change. The second component consists of the auto-regressive associations (ie, T2 regressed on T1, and T3 on T2) capturing the rank-order stability of the variables across the 3 time points (eg, the relationship between cortisol at T1 and T2). The third component typically consists of cross-lagged paths or other hypothesized paths between the variables, accounting for growth factors, and stability factors. In this study, this component will consist of the longitudinal mediation paths (ie, from explanatory variable at T1 to mediator at T2, to outcome at T3). The hypothesized model includes 2 partial mediators of the relation between stressors and child adiposity: child cortisol and behaviors. To test mediation, a direct path from stressors at T1 and child adiposity at T3 is also included. A correlational path between the residualized mediators is also included to model any leftover covariance between them. The fourth component will assess the moderation of the mediated paths. For example, to test the hypothesis that the cortisol mediation may differ across the sex of the children, we can use a multiple groups SEM approach that compares the effect size of mediation across male and female children.

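### Negative life events are totalled over the child's lifetime at baseline but over one year at follow-up, so the totals cannot carry the planned growth slope or T1-to-T2 auto-regression, and the baseline total partly reflects age

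*Protocol article*

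**What the plan says.** Under Chronic Stress: "Chronic stress is assessed using 5 different measures of stress". One of them is an abbreviated List of Threatening Experiences, "an 8-item measure of negative life events" answered yes or no. The primary caregiver reports events "across their lifetime (or for the past year on the follow-up surveys"). One scoring rule covers all waves: "The total score will be determined by summing the number of negative events".

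Under Data Analyses, growth trajectories are fitted to "chronic stressors (explanatory variable), child cortisol and child behavior (mediator variables), and child adiposity (outcome variable"). Each trajectory has "an intercept (I), which refers to a baseline value, and a slope (S), which refers to change over time". Growth components that are not statistically significant are dropped. Auto-regressive paths (T2 on T1, T3 on T2) are added to capture rank-order stability. The mediation paths run "from explanatory variable at T1 to mediator at T2, to outcome at T3", and a direct path runs from the T1 stressors to T3 adiposity.

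The article gives no rule that annualises, cumulates or exempts the life-events total. The Covariates section does not list child age. Under Child Adiposity, BMI is a z score, while waist circumference is described only as a measurement in centimetres.

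**The concern.** A growth slope has meaning only if each wave measures the same quantity on the same scale. Here T1 covers the child's whole life (two to six years or so) and T2 and T3 each cover one year. Three things follow.

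- The slope for this measure mixes any real change in events with the change of window. The expected pattern is also a step followed by a flat line, which a straight line does not fit.
- The T1-to-T2 auto-regression relates a multi-year count to a one-year count. It is not the stability of one quantity and cannot be compared with the T2-to-T3 coefficient.
- Older children have had longer to accumulate events, so the T1 exposure rises with age by construction. Waist circumference also changes as children grow. If age is not adjusted for, part of an association between the T1 count and later waist circumference could be age.

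At stake are a reported decline in child stress that the questionnaire produced, and an age-related component in the exposure end of the T1 paths.

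**Working it through.** The article gives no figure for this measure, so there is none to reproduce. The check asks what the plan's scoring yields when nothing truly changes.

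**Inputs from the article.** Eight yes/no items; lifetime window at T1, one year at T2 and T3; age at entry 2-6 years, mean 3.9 and SD 1.2 (Results); N=300 (Sample Size Estimation), used only to scale the slope.

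**Assumption.** A constant yearly rate L per item, from 0.01 to 0.20.

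**Formulas.** P(yes at T1) = 1 − exp(−L × age). P(yes at T2 or T3) = 1 − exp(−L). The expected score is 8 times the probability. In the rare-event limit the T1/T2 ratio equals mean age, so the fall is 1 − 1/3.9 = 74%. With yes/no items, repeats of an event count once and the score is capped at 8, so the fall is smaller at higher rates.

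**Simulation.** One million children, age truncated to 2 to under 7 years (achieved mean 3.98, SD 1.10, close to the stated values). It was run with one rate for all children (same) and with rates differing between children (gamma, shape 1; differ). The linear slope is (T3 − T1)/2 per child. Its distance from zero is the mean divided by SD/√300.

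| L | T1 mean (same) | T2 mean (same) | T1/T2: same / differ | Fall: same / differ | Slope per year (same) | SEs below zero: same / differ | Correlation of T1 with age: same / differ |
|---|---|---|---|---|---|---|---|
| 0.01 | 0.311 | 0.080 | 3.89 / 3.84 | 74% / 74% | −0.116 | 6.5 / 6.0 | 0.152 / 0.132 |
| 0.02 | 0.611 | 0.159 | 3.85 / 3.74 | 74% / 73% | −0.226 | 9.1 / 8.1 | 0.212 / 0.163 |
| 0.05 | 1.432 | 0.391 | 3.67 / 3.44 | 73% / 71% | −0.521 | 14.0 / 11.5 | 0.314 / 0.202 |
| 0.10 | 2.594 | 0.762 | 3.41 / 3.08 | 71% / 68% | −0.916 | 19.2 / 14.8 | 0.407 / 0.215 |
| 0.15 | 3.535 | 1.114 | 3.17 / 2.81 | 68% / 64% | −1.210 | 22.8 / 17.1 | 0.459 / 0.219 |
| 0.20 | 4.301 | 1.451 | 2.96 / 2.61 | 66% / 62% | −1.425 | 25.6 / 18.8 | 0.491 / 0.215 |

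The fall is 1 − 1/ratio; for example, 1 − 1/2.61 = 62%. T3 means equal T2 means to within 0.001, so the pattern is a step and then flat. With one rate for all children, the true rate would have to rise about 3.9- to 4.0-fold after baseline to hide the fall.

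**Age gradient.** With one rate for all, the expected T1 score at age 6 relative to age 2 is (1 − exp(−6L))/(1 − exp(−2L)). At L=0.01 this is 0.0582/0.0198 = 2.9; at L=0.20 it is 0.699/0.330 = 2.1. With differing rates the expected probability at a given age is L×age/(1 + L×age). The ratio is then 0.0566/0.0196 = 2.9 at L=0.01 and 0.545/0.286 = 1.9 at L=0.20. Age explains 2% to 24% of the T1 variance with one rate for all, and 2% to 5% when rates differ.

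**Same window at every wave.** With a past-year window throughout, the expected slope is 0. The simulated past-year score has a correlation with age of at most 0.001 in absolute value.

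**The case against.** The strongest reply has four parts.

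**Scope.** The article treats the chronic stressors as one explanatory block and does not say whether the five measures enter separately, as a composite or as a latent factor. That detail may sit in the full plan. This stands as a limit on size: in a composite the artefact is diluted. It does not remove the problem, because a component that falls for a mechanical reason still pulls the composite down.

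**Consequence.** No stated hypothesis concerns change in stress. Hypothesis 1 and the mediation paths start from stress at T1, for which a lifetime count is a reasonable measure of chronic exposure. This largely stands. A reader might infer that the fall itself biases the mediation results. The article does not support that: a shift in the mean between T1 and T2 does not by itself bias a regression on T1. The threat to those paths is mainly age.

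**Age.** BMI is already standardised for age, and child age is recorded, so it could be added to the adjustment set in a full analysis plan. The first point weakens the concern for BMI z score. For waist circumference the concern remains on the text as it stands. A reader might also infer that the baseline score is driven by age. It is not: most of its variance lies elsewhere under every assumed rate.

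**Size.** A 74% fall is the rare-event upper end, not a point estimate, and every figure depends on rates the article does not give. This stands. Nor would the score fall in every child, since a child with no events at T1 cannot fall. At the mean age of 3.9 years with one rate for all, that share is exp(−8 × 0.01 × 3.9) = 73% at L=0.01 and exp(−8 × 0.05 × 3.9) = 21% at L=0.05. The fall is one of means.

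**Conclusion.** The concern holds in limited form. The article itself states the change of window, the common scoring rule and a model that needs comparable waves. Followed as written, they give a wrong result for this measure, so this is more than a detail left to another document.

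Under a constant event rate of 0.01 to 0.20 per item per year, the spurious fall in the mean is about 62% to 74%. The false linear slope is large enough at N=300 to survive the plan's rule of dropping non-significant growth components. That significance figure comes from a simple per-child slope in complete data, not from the full structural equation model.

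The T1 score is partly a function of age, and the paths from T1 to waist circumference may be confounded by it. The direction and size of any such bias cannot be computed from the article. The lifetime question at baseline is sound in itself. The defect is treating it as the first wave of a past-year series.

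**What to change.** - Fit no growth slope and no T1-to-T2 auto-regression to the raw life-events totals, whether the measure is used alone or inside a composite.
- Use the T1 lifetime count as a time-invariant baseline exposure, adjusted for child age.
- Use the T2 and T3 past-year counts separately as time-varying exposures. These two share a window and can be compared with each other.

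A running cumulative total (T1 plus each later year's count) is not a good substitute. It can only rise, so it replaces a built-in fall with a built-in non-negative trend, and it keeps the age dependence at T1.

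The cost is small. The article reports that cleaning and analysis are still under way, and the change needs only recoding and respecification of data already collected. The loss is that no three-wave trajectory is estimated for this one measure. The article describes no past-year count at T1 from which one could be built.
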